### Sample size

2.7

#### Pilot study

2.7.1

We conducted a pilot study to evaluate the percentage of women with concurrent urogenital and anorectal *C. trachomatis* infections, in the same population and at the same centers as the trial, to measure the size of the population to be tested. A total of 100 women with a self-collected vaginal swab positive for *C. trachomatis* using NAAT were included and provided self-collected anorectal swabs for *C. trachomatis* detection. Overall, 77.1% (74/96) were positive for anorectal *C. trachomatis*. These results highlight the feasibility of our study.

#### Sample size calculation

2.7.2

We assume rates for successful treatment of anorectal *C. trachomatis* infection of 99% for doxycycline and 83% for azithromycin and a loss of follow-up of 10%. Missing values will be replaced by a failure of the treatment in the intention-to-treat primary analysis. Therefore, to compare 89.1% versus 74.7%, with a 2-sided type 1 error rate of 5% and a power of 90% for a Chi-squared test, the sample size is estimated at 149 patients per group (SAS, proc power v9.3).

According to the pilot study, the prevalence of anorectal *C. trachomatis* infection concurrent with urogenital infection was 75% with 95% confidence interval (95% CI) = (65*–*84%) in our population. For our trial, we made the conservative assumption of a prevalence of 65% of anorectal *C. trachomatis* infection concurrent with urogenital infection at inclusion; therefore, we will include 230 women per group and 460 women in total.

With a total of 460 women enrolled, we will be able to estimate the prevalence of concurrent anorectal and urogenital infections with the following precision:

(1)for a prevalence of 65%: 95% CI = (60.5*–*69.3)(2)for a prevalence of 75%: 95% CI = (70.8*–*78.9)

According to the data of the 7 participating centers in 2015, we have a potential number of 1115 eligible women with *C. trachomatis* positive vaginal specimens.

### Analysis

2.8

Analyses will initially be conducted according to the intent-to-treat principle, with a “missing = failure” strategy for handling missing data on the primary endpoints, in which all randomized participants will be included in the group in which they were first randomized and all their data will be used, regardless of changes over the study duration. For the primary outcome, the failure will be defined as a *C. trachomatis* positive NAAT result for an anorectal swab at week 6, which indicates failure of the treatment.

To check the robustness of the main analysis to missing data, a sensitivity analysis will be performed:

(1)The maximum bias strategy: missing data will be replaced by a failure of the treatment in one group and by a treatment success in the other, and vice versa. Success is defined as a *C. trachomatis* negative NAAT result for an anorectal swab at week 6.(2)An “under treatment analysis” will be performed in which participants will be included in the group according to the treatment they really received, with the available primary endpoints.

If the distribution of baseline prognostic factors is unbalanced between the groups despite randomization, the main and sensitivity comparative analyses will be performed with adjustments to those factors.

For each variable, the number of missing data will be described and the reason for any missing data will be documented as extensively as possible.

All the statistical tests will be performed with a 2-sided type I error rate of 5% and all CIs will be bilateral with a type I error rate of 5%.

Qualitative variables will be described in terms of number, proportion, and exact binomial CI of proportion. Quantitative variables will be described in terms of absolute frequency, mean, standard deviation, CI of the mean, median, minimum, maximum, 1st, and 3rd quartiles.

Descriptive analysis will be overall and by treatment group. Graphical analyses will be associated when possible.

The analyses will be performed using SAS software (version 9.3 or later; SAS Institute, Inc., Cary, NC).

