**Figure 1 F1:**
[figure not shown]
Design of the Chlazidoxy study.

All women with urogenital *C. trachomatis* infection will be included without waiting for the NAAT result of the anorectal specimen because treatment cannot be delayed. However, the study population will consist of only women with both *C. trachomatis* positive vaginal and anorectal swabs.

Information on the need for partner(s) to be treated will be provided. Sexual abstinence or protected intercourse with the partner(s) up to 7 days after the single dose of azithromycin or after 7 days of doxycycline will be recommended (usual recommendations).

The research nurse will complete an electronic Case Report Form (e-CRF) at the time of recruitment of the demographic characteristics (birth date, country of birth, marital status, education level, professional status), and biological (previous *C. trachomatis* infection, HIV-serology, *Neisseria gonorrhoeae* infection, hepatitis B virus, and syphilis serology) and clinical data (vaginal discharge, pelvic pain, abnormal bleeding, pain during sexual intercourse, anal discharge, anal itching, tenesmus). Participants will complete a questionnaire about their sexual behavior [regular sexual partner(s), occasional sexual partner(s) in the last 12 months, use of condoms, anal and oral intercourse] (Table 1).

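### Adjustment of the main comparison, and the covariates used, depend on observed baseline imbalance, and the plan does not say which result then counts

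*Protocol article*

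**What the plan says.** Protocol article, section 2.8 (Analysis), sets a conditional rule: "If the distribution of baseline prognostic factors is unbalanced between the groups despite randomization, the main and sensitivity comparative analyses will be performed". The rule covers the main comparison as well as the sensitivity analyses. The covariates are whichever prognostic factors prove unbalanced ("with adjustments to those factors").

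Section 2.7.2 (Sample size calculation) bases the trial on an unadjusted comparison, "with a 2-sided type 1 error rate of 5% and a power of 90% for a Chi-squared test". It assumes cure rates of "99% for doxycycline and 83% for azithromycin" and counts losses to follow-up as failures; on that basis "the sample size is estimated at 149 patients per group".

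Section 2.5.2 (Randomization) stratifies by investigating centre because the women attending the centres may differ. Section 2.8 does not carry centre, or any other factor, into the comparison as a fixed covariate. The Discussion confirms that participants and investigators know the allocation.

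**The concern.** Section 2.7.2 points to an unadjusted Chi-squared test, while section 2.8 points to an adjusted analysis if certain factors look unbalanced. Nothing says which one carries the conclusion when both exist. If they fall on different sides of 5%, the document offers no rule to decide between them.

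The trigger is also a weak basis for choosing covariates. Under randomization, imbalance arises by chance. Adjustment gains precision according to how strongly a factor predicts cure, and that can be judged before the trial. The size of an observed difference between arms adds little to that judgement.

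At stake is a clear, advance statement of the test and the effect measure on which the trial will be judged. This matters because the Discussion expects the result to bear on treatment recommendations, and because no one handling the data at the centres is blinded to allocation.

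**Working it through.** **1. The plan's own figure.** Inputs from section 2.7.2: cure 99% and 83%, 10% lost and counted as failures, two-sided 5%, power 90%.

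- Rates compared: 0.99 × 0.9 = 0.891 and 0.83 × 0.9 = 0.747. The mean is 0.819 and the difference is 0.144.
- n = [1.96 × √(2 × 0.819 × 0.181) + 1.2816 × √(0.891 × 0.109 + 0.747 × 0.253)]² / 0.144² = 148.1, rounded up to 149 per group. Power at 149 is 90.2%.
- 149 / 0.65 = 229.2, rounded up to 230 per group, or 460 in total.

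The stated sample size is reproduced by the unadjusted Chi-squared test without continuity correction. This point changes none of these figures.

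**2. What the text fixes.**

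| Element | Section 2.7.2 | Section 2.8 |
|---|---|---|
| Test | Unadjusted Chi-squared | Adjusted if factors are unbalanced |
| Covariates | None | Those found unbalanced |
| Which result decides | Not addressed | Not addressed |

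**3. Centre and the trigger.** Stratified 1:1 allocation makes the arms similar by centre among all women enrolled. It does so approximately among those with a positive anorectal swab, who form the analysed population. A rule that adjusts only for unbalanced factors will therefore seldom select centre, although centre is the factor chosen for stratification.

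**4. Effect on type I error.** The document gives neither the number of prognostic factors nor a criterion for imbalance, so both are assumptions here. The null simulation used 298 women (2 × 149), 4,000 runs per scenario, overall cure near 82%, and independent binary factors each present in 40% of women. Imbalance was judged at p < 0.05 or p < 0.20, and adjustment was by logistic regression. Simulation error is about √(0.05 × 0.95 / 4000) = 0.34 percentage points.

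| Factors | Prognostic odds ratio | Threshold | Unadjusted | Rule applied mechanically | Either result claimed | Adjustment triggered | Analyses disagree |
|---|---|---|---|---|---|---|---|
| 10 | 1.0 | 0.05 | 5.2% | 5.0% | 5.5% | 41% | 0.7% |
| 10 | 1.0 | 0.20 | 5.2% | 5.0% | 5.8% | 91% | 1.4% |
| 10 | 1.5 | 0.05 | 5.0% | 4.5% | 5.2% | 42% | 1.0% |
| 10 | 1.5 | 0.20 | 5.4% | 5.3% | 6.1% | 91% | 1.6% |
| 10 | 2.0 | 0.05 | 5.4% | 5.0% | 5.9% | 41% | 1.4% |
| 10 | 2.0 | 0.20 | 4.8% | 4.2% | 5.8% | 91% | 2.5% |
| 5 | 2.5 | 0.05 | 5.4% | 5.1% | 5.7% | 24% | 1.0% |
| 5 | 2.5 | 0.20 | 4.9% | 4.2% | 5.7% | 69% | 2.4% |

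Applied mechanically, the rule stays near or slightly below 5%. If either result may be claimed, the rate is 0.2 to 0.9 points above the unadjusted test in the same runs, and at most about one point above nominal. The two analyses disagree on significance in 0.7% to 2.5% of runs.

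**5. Estimand.** If the adjusted analysis is a logistic model (an assumption, since the article names none), its odds ratio is conditional on whichever covariates were selected. The Chi-squared comparison concerns the marginal cure rates. Under the rule, the quantity estimated depends on which imbalances happened to occur.

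**The case against.** The strongest reply is that the rule looks only at baseline data, is confined to prognostic factors, and does little to the error rate. The simulations bear out the last part. The biologist reading the primary endpoint is blinded to treatment, which protects the measurement, though not the choice of analysis. The list of factors, the criterion for imbalance and the form of the model are details that a condensed article may leave to the full protocol or analysis plan, so their absence is not held against this document. What remains is the rule itself. It is stated here, and an analysis plan could not fix one covariate set regardless of balance without contradicting it.

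The text does not support several stronger readings that a reader might infer:

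- **That the main analysis is switched, or that no confirmatory test exists.** Section 2.7.2 names an unadjusted Chi-squared test, and section 2.8 does not say that an adjusted result displaces it. The defect is the unclear standing of the adjusted result.
- **That the 5% error rate is seriously broken.** The figures above show otherwise.
- **That adjustment is more likely than not.** Section 2.5.1 begins its list of recruitment data with "The research nurse will complete an electronic Case Report Form (e-CRF) at the time of recruitment of the demographic characteristics", and about 22 variables can be counted there, giving 1 − 0.95^22 = 68% for at least one imbalance. That treats all of them as prognostic, independent and tested at 5%, none of which the document says. It is also a chance of triggering adjustment and says nothing about false positives.
- **That the choice will be made with outcomes in hand.** No timing is stated. The text neither provides for this nor rules it out.
- **That moving the sensitivity analyses together with the main one is a flaw.** Two missing-data analyses run under the same model as the main analysis isolate the missing-data question, which is sensible.

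**Conclusion.** The concern stands as a matter of prespecification. Section 2.8 lets chance imbalance decide whether the main comparison is adjusted and for what, and leaves open which result counts. The trigger tends to pass over centre, and the effect measure may shift with the covariates selected.

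The numerical consequence is small: type I error of 4.2% to 5.3% under mechanical use, and 5.2% to 6.1% if either result can be claimed. These figures rest on 5 or 10 independent binary factors, the two assumed thresholds and a logistic model. They do not cover a freer search over criteria or covariate sets. The sample size of 149 per group and 460 in total is unaffected. The point is worth correcting before analysis but does not undermine the trial.

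**What to change.** Remove the imbalance trigger from the main analysis in section 2.8. State one primary comparison that is applied whatever balance is observed. A centre-stratified Mantel-Haenszel test with a risk difference would suit the randomization; other fixed choices are acceptable. A short list of prognostic covariates may be added if it is settled before any outcome data are seen. Run the missing-data sensitivity analyses with that same model. Label any adjustment prompted by observed imbalance as supportive and unable to replace the primary result.

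The cost is about one sentence of text and slightly less freedom to respond to a chance imbalance. Nothing changes at the centres, and no new sample size follows.

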### Ethics approval

2.9

The Chlazidoxy trial has been approved by the French ethic Committee for the Protection of Persons (“Comité de Protection des Personnes”) (CPP) on February 14, 2018 (CPP number 2017-74-2). This trial was authorised by the French National Agency for Medicines and Health Products Safety (“Agence Nationale de Sécurité du Médicament et des Produits de Santé”) (ANSM) on January 26, 2018 (reference IDRCB 2017-002595-15). All participants in the study will sign an informed consent form before participation.

In case of a modification to the protocol, the investigator-coordinator is expected to submit a request to the CPP and send an information note to all the investigators.

### Trial governance

2.10

#### Sponsor

2.10.1

The Chlazidoxy trial is sponsored by the Bordeaux University Hospital.

Bordeaux University Hospital is involved in the implementation of the trial, legal/ethical submissions, and hosting of the Chlazidoxy database. It is not involved in the design of the study, analysis, or interpretation of the data. Bordeaux University Hospital is also in charge of regular quality control assessments. A clinical research assistant will visit participating centers to ensure that implementation is in accordance with the protocol.

Bordeaux University Hospital has taken out insurance from HDI-GERLING through BIOMEDIC-INSURE for the full research period, covering its own civil liability and that of any agent (doctor or research staff), in accordance with Article L.1121-10 of the French Public Health Code.

#### Coordinating unit

2.10.2

Bordeaux University Hospital and the Bacteriology department are responsible for coordinating this trial. They will ensure that recruitment and follow-up are performed as planned.

#### Investigating centers

2.10.3

CeGIDD and pregnancy termination centers are involved in the recruitment, inclusion, and follow-up of the participants. They collect informed consent from the participants and implement randomization. They are responsible for notify the sponsor's vigilance division of any adverse event by filling in the adverse event section of the e-CRF.

#### Steering committee

2.10.4

The steering committee comprises coordinating investigators, scientific experts, a methodologist and biostatistician, and representative of the sponsor. The Scientific Committee of the study meets before the beginning of the inclusions, at the end of the inclusions, at the end of the study, and according to the needs defined by the promotor and the coordinating investigator. The steering committee will be responsible for inquiring about research progress, monitoring compliance with good clinical practice and patient safety, deciding on any relevant modification of the protocol, and monitoring compliance with the rules of communication and publication of the results described in the protocol.

#### Data monitoring committee

2.10.5

The present study does not require an independent data monitoring board, given that both investigational drugs are already recommended at the same dosage by the French Authority for Public Health as the treatment of choice for chlamydia infections.

## Discussion

3

Given the high prevalence of anorectal *C. trachomatis* infection concurrent with urogenital infection, it is important that the most efficacious treatment is used. Currently, as anorectal screening is not widely recommended in women with urogenital infection, azithromycin, which fails in 17% of cases according to meta-analysis, continues to be largely used. These findings suggest that many anorectal infections are suboptimally treated with azithromycin, which could be a potential obstacle in the control of *C. trachomatis* transmission and its complications. This will be the first RCT to compare azithromycin and doxycycline for concurrent anorectal and urogenital *C. trachomatis* infections in women and will establish whether doxycycline is more efficacious than azithromycin. If azithromycin efficacy is indeed 83%, then this is much lower than the 95% threshold recommended by the World Health Organization for STI treatment and it should not be used for rectal *C. trachomatis.*^[25]^ The ability to differentiate between treatment failure and reinfection using highly discriminative molecular methods is a major strength of this study.

We originally planned to realize this RCT as double-blind to ensure that the risk of reinfection was similar between treatment arms; it is possible that taking a daily dose (as is required for doxycycline) may deter people from resuming sexual activity while undergoing treatment.^[26]^ However, because of drug manufacturing reasons, we will have to conduct this study as an open-label RCT. Indeed, the treatments administered are those recommended by the French National Authority for Health and are very well accepted by all the patients; in addition, patients will be randomized with a 1:1 ratio. Both participants and investigators will have knowledge of the treatment arms. Despite the absence of blinding, the biologist performing the bacteriological analyses on the primary outcome will be blinded to the drugs taken by the participants, thus limiting the possibility of bias.

If our study reveals that doxycycline is more effective than azithromycin in treating anorectal *C. trachomatis* infections, the current recommendations for the treatment of urogenital *C. trachomatis* infections could be revised, taking into account a concurrent anorectal infection. The results of this study could challenge the consensus treatment consisting of a single 1 g dose of azithromycin in the case of uncomplicated urogenital infections. This may be restricted to use in urogenital infections without concurrent anorectal infection.

If our study is conclusive, an alternative strategy for *C. trachomatis* control would be to curtail the use of azithromycin. Moreover, azithromycin has the disadvantage of promoting resistance to macrolides of *N. gonorrhoeae* and *Mycoplasma genitalium*, the bacteria responsible for STIs that may be associated with *C. trachomatis*. Finally, the ultimate recommendation could be to treat *C. trachomatis* only with doxycycline, as was proposed for the control of gonorrhea and chlamydia in the United Kingdom in the past^[27]^ and as recommended in the European guidelines on *M. genitalium* infections published in 2016.^[28]^
